## Abstract

**Introduction:**

Cerebral palsy (CP) affects up to 4 children in 1,000 live births, making it the most common motor disorder in children. It impairs the child’s ability to move voluntarily and maintain balance and posture, and results in a wide range of other functional disorders during early development impairments in various sensory modalities, e.g., vision, hearing ability and proprioception. Current standard of care therapy focuses on symptom management and does not mitigate the progression of many of these underlying neurological impairments. The goal of this trial is to conduct a prospective multicenter, double-blinded, sham-controlled, crossover, randomized control trial to demonstrate the safety and efficacy of noninvasive spinal cord neuromodulation (SCiP™, SpineX Inc.) in conjunction with activity-based neurorehabilitation therapy (ABNT) to improve voluntary sensorimotor function in children with cerebral palsy.

**Methods and analysis:**

Sixty participants (aged 2–13 years) diagnosed with CP classified as Gross Motor Function Classification Scale Levels I-V will be recruited and divided equally into two groups (G1 and G2). Both groups will receive identical ABNT 2 days/wk. G1 will initially receive sham stimulation, whereas G2 will receive therapeutic SCiP™ therapy for 8 weeks. After 8 weeks, G1 will cross over and receive therapeutic SCiP™ therapy for 8 weeks, whereas G2 will continue to receive SCiP™ therapy for another 8 weeks, for a total of 16 weeks. Primary and secondary outcome measures will include Gross Motor Function Measure-88 and Modified Ashworth Scale, respectively. Frequency and severity of adverse events will be established by safety analyses.

**Ethics and dissemination:**

The trial is registered on clinicaltrials.gov (NCT05720208). The results from this trial will be reported on clinicaltrials.gov, published in peer-reviewed journals and presented at scientific and clinical conferences.

## Background

Cerebral palsy (CP) is the most common childhood motor disorder, with an estimated 1 in 345 children identified with CP within the United States. It has a global incidence of 17 million and approximately 800,000 individuals are currently living with CP in the U.S. (Oskoui et al., 2013). CP results in weakness, delayed motor development, significant motor impairment ranging from weakness in one hand, to an almost complete lack of voluntary movement in all four limbs. The most common presentation of CP is spastic CP, which is diagnosed in early childhood (Novak et al., 2017; te Velde et al., 2019). However, CP is a lifelong debilitating condition resulting from permanent damage to the developing brain (Flett, 2003). Even though the initial abnormal brain development resulting in CP is not progressive, the cascade of motor impairments that evolve during childhood persists and can worsen into adulthood, reducing the quality of life of the affected individuals and their family members/caregivers (Frisch and Msall, 2013). While the specific causes of CP are often unknown, changes in blood flow, maternal infections, intrauterine stroke, injury, or genetics are common causes. Compared to typically developing children, the medical care costs are 10 times higher for the children with CP, with the estimated lifetime care costs for an individual with CP exceeding $1 million (Kruse et al., 2009).

Currently, there are no treatments for CP that mitigate the underlying neurological dysfunction to enable voluntary movement. The treatment regimen is often individualized, depending on specific needs, severity of symptoms, and affected body parts. Regardless, a primary standard of care tenet for most individuals is activity-based neurorehabilitation therapy (ABNT), potentially with subsequent medication to manage pain and spasticity and/or surgery to relieve symptoms of spasticity. Surgical procedures such as selective dorsal root rhizotomy (SDRs) are often successful in decreasing spasticity, but has limited impact on recovery of voluntary sensorimotor function (Tedroff et al., 2015). Although early intervention with aggressive treatments may promote functional recovery via symptom management, they cannot reverse the neurological damage. Therefore, there is an unmet clinical need in the current clinical care, which is primarily focused on management of symptoms and maintenance of the persistently impaired functional states.

## Proposed solution

To address this need, SpineX Inc. has developed a noninvasive spinal neuromodulation device SCiP™ (Spinal Cord Innovation in Pediatrics), a Class II, Nonsignificant Risk Device, recognized with a breakthrough device designation by US FDA for treating the underlying condition associated with CP. SCiP™ directly modulates the spinal cord neural circuits and indirectly the supraspinal neural circuits by transcutaneously delivering novel electrical pulses below motor thresholds to neuromodulate spinal and supraspinal networks into an activated state of plasticity. Although the exact mechanisms by which transcutaneous electrical spinal neuromodulation transforms the spinal neural networks into more functional states is not fully understood, considerable insights have been gained from studies of spinal cord injury and other forms of paralysis (Edgerton et al., 2021). Our initial findings demonstrated that acute (single session) neuromodulation with SCiP™ in children with CP significantly improved the postural and locomotor abilities in 11 out of the 12 participants (Gad et al., 2021).

In the chronic approach, we combined neuromodulatory (SCiP™) and rehabilitative (ABNT) strategies (Hastings et al., 2022). In our pilot trial, 16/16 children (age 2.5–16) who received SCiP™ therapy in conjunction with ABNT for 8 weeks, demonstrated significant motor recovery. Their Gross Motor Function Measure-88 (GMFM88) scores improved by 13.3 ± 1.3 points (*p* < 0.05), more than twice the minimal clinically important differences (MCID) of 5 points (Storm et al., 2020), and greater than other available treatment options. Functional improvements persisted even in the absence of active stimulation, supporting our working hypothesis that spinal neuromodulation facilitates targeted spinal-supraspinal neural plasticity needed for long-term recovery.

Our hypothesis is that first we neuromodulate the neural networks to an elevated state of plasticity. The second stage of the transformation is to provide activity dependent mechanisms to guide the transformation of the neuromodulated networks to more functionally competent states, depending principally on specific activity dependent guidance derived from specific patterns of proprioception. All data to date from studies from individuals with severe spinal cord injuries (Shackleton et al., 2022) and from our initial studies of CP (Hastings et al., 2022) are consistent with this hypothesis. The potential for neural plasticity, theoretically and with a considerable number of scientific studies (Tang et al., 2019), suggests that there is greater plasticity at younger age (Johnston, 2004). Thus it is imperative to consider the potential advantage of timely and adequate intervention for maximal efficacy in this population. Another factor that shapes the design of the proposed trial protocol is the extreme heterogeneity in severity of neurological impairment in CP, which produces differential functional capabilities within these children. For instance, children with Gross Motor Function Classification System (GMFCS) levels I, II and III are capable of performing tasks such as dynamic standing, overground walking, treadmill stepping and backward walking, whereas children with GMFCS levels IV and V require significant external assistance and training in sitting, trunk and postural activities with minimal treadmill stepping and no backward or overground stepping. Therefore, the ABNT protocol needs to be tailored to accommodate the functional capabilities of these children.

## Trial objectives

The primary objective is to assess the safety and efficacy of 8 weeks of SCiP™ therapy during ABNT compared to sham (inactive) neuromodulation during ABNT in improving voluntary sensorimotor function measured on the GMFM88 scale in children with CP. The secondary objective is to assess the safety and efficacy of short-term (8 weeks) vs. long-term (16 weeks) SCiP™ in conjunction with ABNT in improving voluntary sensorimotor function (GMFM88 score). We hypothesize that children who undergo SCiP™ neuromodulation therapy in conjunction with ABNT will demonstrate a statistically greater improvement in voluntary sensorimotor function as assessed by GMFM88 scores, compared to subjects undergoing sham modality in conjunction with ABNT. The proposed clinical trial was discussed with the US FDA via a virtual sprint discussion owing to the breakthrough device status; and SpineX and the agency have reached an alignment on the clinical trial design, primary and secondary outcomes, sample size and safety outcomes.

## Methods and analysis

### Study design and setting

The trial overview is in accordance with SPIRIT guidelines (Chan et al., 2013), and is illustrated in Table 1. Study participants, their parents/caregivers and physical therapists were involved in study design, choice of ABNT and design of SCiP™ device. The study is designed in three phases:

Phase I: a primary prospective, multicenter, double blind, two-arm, randomized (1:1) sham controlled clinical study through 8 weeks.Phase II: Upon completion of the randomization phase, subjects have the option to enter a secondary non-blinded observation treatment extension phase through 16 weeks.Follow-up phase: All patients will be reassessed 8 weeks after the last stimulation session as a follow-up to assess the level of functionality retained.

**Table 1 tab1:** The schedule of enrolment, interventions, and assessments based on SPIRIT guidelines.

Activity	Phase I				Phase II		Follow-up
	Screening	Baseline Visit 0	Visits 1 to 16	Primary eval. visit 17	Optional extension visits 18–33	Extension eval. visit 34	Follow-up eval. visit 35
Informed consent	X						
Eligibility assessment	X						
Physical examination	X						
Vital sign assessment	X	X	X	X	X	X	X
Medical history, demographics, medication history	X						
Concomitant medications	X	X	X	X	X	X	X
GMFM88		X		X		X	X
MAS		X		X		X	X
10MWT (GMFCS levels I-III only)		X	X	X	X	X	X
GMFM88 dimension B (GMFCS levels IV-V only)			X		X		
PBS		X		X		X	X
PEDI-CAT		X		X		X	X
PAICP	X	X	X	X	X	X	X
Randomization		X					
Electrode placement; identification of stimulation parameters		X					
Stimulation or sham with ABNT			X		X		
Adverse events		X	X	X	X	X	X
Device deficiencies		X	X		X		
User experience questionnaire				X		X	X
Bang blinding assessment				X			

Up to 10 investigational sites will participate in the study. Investigational sites will be identified and selected based on qualifying criteria, including the volume of targeted subjects who would meet eligibility for study inclusion. No site will contribute more than 35% of the total number of randomized subjects (included in the analysis set). ABNT, Activity Based Neurorehabilitation Therapy; GMFM88, Gross Motor Function Measure; MAS, Modified Ashworth Scale; 10MWT, 10 Meter Walk Test; PBS, Pediatric Balance Scale; PEDI-CAT, Pediatric Evaluation of Disability Inventory Computer Adaptive Test; PAICP, Pain Assessment in Cerebral Palsy.

Children will be observed for up to approximately 30 weeks. This includes an initial washout period of 2 weeks, Screening visit, a Baseline (Visit 0), Phase I (Visits 1–16 of approximately 60-min therapy sessions twice a week for 8 weeks), a Phase I post 8-week evaluation (Visit 17), Phase II (Visits 18–22), an 8-week treatment extension in which the sham group will receive treatment and treatment group will receive an additional 8 weeks of treatment, a Phase II post 8 or 16-week evaluation (Visit 34) occurring within 1–3 days of the last session, and a follow up evaluation 8 weeks post last intervention (visit 35, at week 24). During the washout period, all children will be asked to stop all antispastic medications and other forms of therapies including hippo therapy, intensive therapies etc. A clinical trial outline has been described in Figure 1.

**Figure 1 fig1:**
[figure not shown]
Clinical trial timeline. Following a 2 week washout period, the treatment and sham groups receive therapeutic stimulation or sham stimulation, respectively, for 8 weeks. After the primary evaluation on visit 17, sham group will cross over to begin 8 weeks of therapeutic stimulation, similar to the treatment group that will continue with another 8 weeks of therapy for a total duration of 16 weeks. Following the extension evaluation at visit 34, the participants will receive no intervention for 8 weeks. After 8 weeks of no intervention, participants will return to the clinic for a follow-up evaluation at visit 35 (SCiP ™, Spinal Cord Innovation in Pediatrics; ABNT, Activity Based Neurorehabilitation Therapy).

### Study population and recruitment

Up to 80 participants (ages ≥2 and ≤ 13 years), diagnosed with CP, spastic diplegia, spastic hemiplegia or spastic quadriplegia, and GMFCS Level I-V will be consented to achieve a minimum of 60 evaluable datasets (30 treatment, 30 control) at the primary Phase I endpoint of 8 weeks (see statistical analysis for sample size calculation). The inclusion/exclusion criteria are described in Supplementary Table S1.

### Randomization and blinding

Participants will be randomized into a treatment (SCiP™) arm and control (sham) arm in a 1:1 ratio. A block randomization technique will be employed, and randomization will be stratified by age (2–7 and 8–13) and GMFCS level (levels stratified as I + II + III & IV + V; ambulatory and non-ambulatory groups). All participants and the clinicians administering the assessment will be blinded to the initial group assignment. The sham device will be physically identical and intensity on the LCD display will be shielded from the participants. At Phase I primary evaluations, participants will be asked what treatment they believe they received using the Bang blinding index (Bang et al., 2004). Participants will not be blinded during the Phase II, open label extension during which all subjects will receive SCiP™ treatment.

### Intervention

The SCiP™ device is a non-invasive electrical neuromodulation device designed to provide transcutaneous spinal cord neuromodulation through the skin (Figure 2). SCiP™ consists of (1) SCiP™ Device, (2) one electrode cable assembly, and (3) four electrodes (one circular electrode placed on cervical, 1.25″ diameter, Axelgaard) and thoracic spine (1.25″ diameter, Axelgaard) and two rectangular electrodes on the hips (2 × 4″, Axelgaard). SCiP™ device uses advanced waveforms that emit a lower overall power density compared to contemporary devices. This allows the pain-free administration of electrical stimulation directly to the spinal cord neural networks (cervical levels C5-6 and thoracic levels T11-12), in order to modulate the circuitry that controls sensorimotor functions of the upper limbs, trunk and lower limbs.

**Figure 2 fig2:**
[figure not shown]
Depiction of wearability and form-factor of Spinal Cord Innovation in Pediatrics (SCiP™) unit and electrodes placement on a child.

Participants randomized to the therapeutic group will receive transcutaneous neuromodulation via SCiP™ device. The motor threshold will be determined by the therapist via a visible motor contraction of paraspinal, abdominal, upper or lower extremity muscles induced by the stimulation. During training, a sub-motor threshold intensity will be used to ensure no motor evoked responses are generated (muscle contractions) and that the stimulation does not result in pain or discomfort. The stimulation will begin at 0 mA and will be increased by 1 mA every 10 s within sub-motor threshold intensity. Intensities over the C5-6 spine will range between 6 and 20 mA and over the T11-12 between 5 and 16 mA based on the activity being performed and subject-specific responsiveness. Initial stimulation amplitude will be set when the participant voluntarily attempts to extend the cervical or thoracic regions while in a seated position. Based on our preliminary observations, the amplitude will be lowered by 1–2 mA during activities involving sitting, rolling etc., and increased by 2–4 mA during standing and stepping. The intensities will be modulated ±2 mA based on the functional performance of the participant and the sensory perception skills of the therapist during the task.

Participants randomized into the sham group will not receive active electrical stimulation. However, to ensure sufficient blinding, during each session, with the child in a seated position, stimulation will be delivered at C5-6 and T11-12 at an intensity of 1 mA for a period of 1 min. After 1 min, the stimulation will be automatically decreased to 0 mA, however, the SCiP™ device will continue to make a beeping sound mimicking a therapeutic stimulation session. To ensure consistency across multiple sites, all site personnel will be thoroughly trained and provided with a written guidebook.

The participants in both groups will receive ABNT, which is designed based on our preliminary investigations (Hastings et al., 2022), i.e., input from expert pediatric physical therapists, the severity of impairment, acceptability of the subject and caregiver and collaboration with participating study centers. This was done to ensure the uniform inclusion of current standard of care practices and accommodation functional capabilities of individual child. Table 2 describes various ABNT activities based on the GMFCS levels. During ABNT, the goal will be to maintain appropriate posture, midline orientation and head position with center of mass over base of support for optimized weight bearing to organize proprioceptive information. ABNT sessions will be video recorded and analyzed by the contract research organization to ensure consistent delivery of stimulation protocols.

**Table 2 tab2:** Description of the ABNT activities based on the GMFCS levels.

#	Approx. time (mins)	Step	GMFCS level	Activity description
**1**	10	Treadmill stepping	All	At speeds from 0.1 to 3.0 mph. Start at slowest speed (0.1 mph), for 3 min, then try to get as high as the child can move their legs. Note: Therapist may need help to advance and to encourage child’s self-initiation. Body weight support (Harness) will be used as needed
**2**	5	Assisted backwards treadmill walking	All	At speeds from 0.1 to 0.3 mph. Therapist may need help to advance and to encourage child’s self-initiation. BWS (Harness) will be used as needed
**3**	5	Side-stepping over level ground	I-III	Have child positioned near wall or a waist high table and perform and activity incorporating side-stepping. Children should take at least 3–4 steps in each direction keeping hips and feet pointed toward wall or table
**3**	5	Sitting: trunk posture and head control	IV-V	Have the child be seated on a bench with the heel on the ground. Their trunk should be maintained in alignment with head, shoulders, and hips in one line.
**4**	5	Functional play running	I-III	Have child run by playing a game that has them run fast and then immediately stop when a verbal cue is given (e.g., games such as Red Light, Green Light, or Mother May I?)
**4**	5	Rolling	IV-V	Have the child in supine position on a mat. Introduce a toy and encourage the child to reach over to that side with their hands and legs
**5**	10	Sit-to-stand transitions and reaching	All	Activity involves an upper extremity activity (usually reaching for a toy) which requires the child to stand. Both hands should be used equally with one-hand and two-hand activities
**6**	10	Jumping and climbing with descending	I-III	Have child ascend and descend 6-inch steps using only legs with therapist assisting as needed.
**6**	10	Half kneel to stand	IV-V	(1) Position the child on all fours (quad kneeling) (2) Child should transition from half knee to standing. They may use their hands on a surface if needed.
**7**	5	Treadmill walking	All	Have child walk on treadmill with good form (i.e., head, hips and heel in one vertical line and heels touching the treadmill belt during initial contact) at slowest speed (0.1–0.3 mps) either independently or the least amount assistance

All participants will be required to discontinue, for 14 days prior to consent and for the duration of their participation in the study, other ongoing physical and occupational therapies, including but not limited to robotic therapy, gait training, aqua therapy, hippo therapy, intensive therapies, whole body vibration, and electrical stimulation therapies.

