### Sample size and power

We assume a true sham responder rate of 0.22 or less, and a treatment responder rate of 0.68 or higher, based upon pilot study observations and assuming 10% attrition of participants during the study. Thus, a sample size of 60 will support 80% power to distinguish between the arms, in a two-sided exact test at the 0.05 significance level. Considering the heterogeneity of prospective participants, proposed sample size of 60 participants (30 per arm) will ensure 80% power for primary endpoint comparison, allowing for precise estimation of responder rates in different demographic subpopulations. Assuming 25% attrition rate of participants in screening based on pilot study, the required number of participants to be screened is 80. The proposed sample size is consistent with other similar studies (NCT05020834, NCT04725019, NCT05154253, NCT05351138).

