
## Data management and safety

Parents and/or legal guardians of all eligible participants will be invited to discuss the protocol and its risks and benefits with the site Principal Investigator (PI). Parents and/or legal guardians of potential participants will be given at least 72 h and will be encouraged to read the informed consent, and discuss the study with their child, physician, family, and friends, before signing the IRB-approved informed consent. The informed consent forms will be written in a language understood by an eighth-grade student and will contain information on all outcomes as well as PI’s contact information. IRB-approved age-appropriate assent forms will be provided to minors, based on considerations such as the age, maturity, and degree of literacy. Assent from pre/non-literate children will be obtained in accordance with local IRB requirements.

The original signed informed consent (and assent, if applicable) and two copies will be kept in the PI’s office. No participant will be allowed to enroll without being examined by site PI. The participants will be monitored closely to assess for evidence of complication from experimental protocol. The data monitor, clinical research operations team and medical monitor will closely monitor the participants in regards to the procedures and will be available for consultation.

During training, every participant will be slowly acclimated to the treadmill and other devices. Vitals will be monitored (blood pressure, oxygen saturation, heart rate, pain scores) at each session. Stimulation will be stopped in case of an adverse event during and the participant will receive appropriate standard of care treatment. Before and after every session, a physical therapist will examine the participant’s skin for irritations and abrasions. If skin irritations or abrasions are caused by the recording electrodes or hand placements of trainers, electrode and hand placement will be modified. Furthermore, the therapist will monitor the participant’s skin and muscle for signs of muscle strain, joint sprain, and skin irritation (e.g., temperature and redness). The therapist will assess the appropriate lower extremity parameters and monitor manual assistance by trainers to avoid joint sprain. The physical therapist or trained staff member will stretch the muscles of the participants before and after each training session to prevent injury. PAICP will be completed at every session to monitor for pain signs.

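### As written, therapies must stop for 14 days before consent, so a study-directed withdrawal comes before the guardian's signature and the screening examination

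*Protocol article*

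**What the plan says.** The rule stands in the paragraph after Table 2, at the end of the Intervention section of the protocol article: "All participants will be required to discontinue, for 14 days prior to consent and for the duration of their participation in the study". What must be stopped is other ongoing physiotherapy and occupational therapy, with a non-exhaustive list that includes robotic, gait, aquatic and electrical stimulation treatments.

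The section on study design and setting describes the same two weeks as part of the study: "Children will be observed for up to approximately 30 weeks. This includes an initial washout period of 2 weeks, Screening visit", followed by Baseline (Visit 0) and the two treatment phases. It adds: "During the washout period, all children will be asked to stop all antispastic medications and other forms of therapies".

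Table 1, the schedule of enrolment and assessments, marks informed consent, eligibility assessment, physical examination and medical and medication history in the Screening column only. Adverse events are first marked at Baseline (Visit 0). The table has no washout column. The Figure 1 caption says: "Following a 2 week washout period, the treatment and sham groups receive therapeutic stimulation or sham stimulation, respectively, for 8 weeks".

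The section on data management and safety describes one consent process, in which guardians "will be given at least 72 h and will be encouraged to read the informed consent" before they sign. It also makes examination by the site's principal investigator a condition of enrolment.

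**The concern.** A washout that the study imposes is a study procedure. The normal order is signed consent, then screening, then any withdrawal of treatment. Here the 14 days are counted back from consent, so the withdrawal would be complete by the time the guardian signs.

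At stake is the protection of children with cerebral palsy who rely on regular therapy. They would interrupt it for a trial that nobody has yet agreed to on their behalf, and before the investigator has examined them. The protocol also expects a substantial loss at screening: "Assuming 25% attrition rate of participants in screening based on pilot study, the required number of participants to be screened is 80". In the written order, a child on therapy who is then found ineligible at Screening has already stopped. With screening first, that child would not be asked to stop.

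**Working it through.** No sample size or error rate bears on the order of events, so the check sets the statements side by side.

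1. **Anchor of the 14 days.** The Intervention section counts them back from consent, not from Baseline or first stimulation.
2. **Who directs the stop.** The Intervention section makes it a requirement and applies it to therapies that are ongoing. The study design section says children are asked to stop. Both describe an instruction from the study.
3. **When consent and examination happen.** Table 1 places both at Screening and nowhere earlier.
4. **Any earlier consent step.** The section on data management and safety describes a single process and no separate consent for the washout.
5. **Resulting order.** Day −14: therapies stop. Day 0: consent, with eligibility assessment and physical examination at the same Screening stage. Then Baseline (Visit 0) and randomisation.
6. **Agreement elsewhere.** The list of periods in the study design section puts washout before Screening, which is the same order. The Figure 1 caption only requires washout to precede stimulation, so it fits either order.
7. **Medication.** The Intervention sentence names therapies only. Antispastic drugs appear only in the study design section, whose place for the washout relative to consent rests on list order.

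Two checks on the alternative order (consent and screening, washout, Baseline):

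- **Length.** Washout 2 weeks, Phase I 8, Phase II 8, follow-up 8: 2 + 8 + 8 + 8 = 26 weeks. Against approximately 30 weeks of observation this leaves about 30 − 26 = 4 weeks for screening and visit windows.
- **Baseline measurement.** Table 1 takes GMFM88 and MAS at Visit 0, not at Screening. Both would still be measured after the washout.

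**The case against.** The strongest reply is that the sentence may be only an eligibility look-back: a child qualifies if no other therapy was received in the previous 14 days. The criteria are in Supplementary Table S1, which is not shown, and the article condenses a fuller protocol. This reading cannot be excluded. It fits the wording poorly, though. A look-back would say that the child has not received therapy, whereas this sentence requires ongoing therapies to be discontinued, and the same clause continues through the whole of participation.

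A second reply is that the study design section is weak support, and that is fair. The order rests on one list, and the same sentence gives Phase II as Visits 18–22 (5 visits), where Table 1 has 18–33 (16 visits, matching twice a week for 8 weeks). It also counts the washout within the period of observation, which would suit children already consented. The reference to consent in the Intervention section may therefore be a slip for Baseline. That would explain the sentence, but the sentence would still need correcting.

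A reader might go further in four ways that the documents do not support:

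- **Antispastic drugs are withdrawn before consent.** No sentence says so; it follows only from list order.
- **Therapy stops before the guardian has the consent form.** The 72 hours is a minimum, and nothing says when sites hand the form over.
- **The 25% screening loss can be turned into an amount of therapy lost.** The documents do not say how many of those children were on therapy, stopped it for the study, or were lost at Screening itself.
- **Harms during the washout go unrecorded.** Adverse events are first marked at Visit 0, but the period that visit looks back over is not stated. Vital signs, concomitant medication and the pain instrument are already marked at Screening.

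**Conclusion.** The point holds as a fault in the written rule. Read with Table 1, the Intervention section places a 14-day, study-directed withdrawal of therapies before the guardian's signature and before the screening examination. It should be fixed because the participants are young children and the change is small.

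Confidence is medium. The conclusion assumes that the sentence means what it says and that Supplementary Table S1 does not recast it as a look-back. Whether sites would follow it literally cannot be judged from this document.

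The stated size is the 14 days; the number of children affected cannot be derived. No effect is claimed on the randomised comparison, the responder criterion or the later analyses, since the rule applies to both arms before randomisation.

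**What to change.** - **Intervention section:** count the 14 days back from Baseline (Visit 0) instead of from consent.
- **Study design section and Table 1:** set the order as signed consent and screening examination, then the 14-day washout, then Baseline. Add a washout column to Table 1. State that the same order applies to antispastic medication, which removes the need to infer it.
- **Table 1:** mark adverse events from consent, so that the washout is covered.
- **If a look-back is intended:** say so in the eligibility criteria, and state that no family is to be asked to stop therapy in order to qualify before consent.

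The cost is a wording and schedule amendment and some additional adverse-event recording. The analysis does not change. The one real downside concerns recruitment. Up to 80 children "will be consented to achieve a minimum of 60 evaluable datasets (30 treatment, 30 control" at the 8-week endpoint, and drop-outs during washout would now occur after consent and count against those 80. At the stated screening loss, 80 × (1 − 0.25) = 60, which leaves no reserve if washout losses come on top of the 25%. The protocol gives no washout loss rate, so the sponsor should say whether the 25% includes it and review the ceiling of 80 accordingly.
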